### Recruitment

Recruitment will be done by the surgeons / gynecologists of the breast unit. Every woman diagnosed with breast cancer is referred for surgery. In it, the surgeon will identify the patients who meet the inclusion criteria.

Recruitment began when the Hospital’s ethics committee approved the study. therefore, the registration and publication of the protocol has been carried out later.

### Retention

The assessment and follow-up of the participants included in the study was carried out in the consultations usually scheduled for follow-up and treatment. In this way, patients do not usually leave the study.

### Statistical analysis

We will conduct a descriptive analysis of the variables included in the study. All quantitative variables will be expressed with the mean, standard deviation and corresponding 95% confidence interval. Comparison of proportions: The differences between the various qualitative variables will be found using Fisher’s exact test or the chi-squared test (χ2). The qualitative variables will be expressed in proportions and respective confidence intervals. The differences between the quantitative variables will be analyzed using Student’s t-test for independent groups. If the conditions of the t-test are not verified, we will use the Mann-Whitney U test. We will use Kaplan-Meier curves and compare them using the log-rank test to determine those variables related to locoregional relapse and the incidence rate of new tumors, as well as to assess cosmetic deterioration. The statistical analysis will be performed using version 24 of the statistical program IBM SPSS and Epidat 4.1.

Patients with missing data will be exclude for the analysis.

The analysis of the safety of the surgical technique will be performed on the entire sample. Oncological safety and satisfaction assessment will be analyzed by groups: oncological patients and patients with a RRM.

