### Study objectives

#### Main objective

To evaluate the safety of prepectoral reconstruction in terms of postsurgical complications and the feasibility of reconstruction (implant loss).

Secondary objectives:

To evaluate the safety of sparing mastectomy through the identification of RGT, primary carcinomas and breast cancer relapses (patients operated on for breast cancer).To assess satisfaction and quality of life after prepectoral reconstruction in women with breast cancer and those with high risk.To identify factors related to satisfaction and quality of life after prepectoral reconstruction.To evaluate the cosmetic sequelae after prepectoral reconstruction in women with breast cancer and with high risk.To identify factors related to the cosmetic sequelae after prepectoral reconstruction.

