Postoperative bleeding is defined as the appearance of any amount of bleeding that modifies the course of the first 7 postoperative days. Among these modifications we find: the need to prolong admission due to blood drainage and the need for reoperation due to bleeding or hematoma. Superficial ecchymoses that do not modify the immediate postoperative period are not includedSkin necrosis is defined as the appearance of areas of skin without vascularization that condition cell death. Necrosis that appeared during the first 3 months after surgery that conditioned some action by the surgeon are included.Within the necrosis of the nipple areola complex, only deep necroses that required some surgical interventions are included.Seroma is defined as the accumulation of periprosthetic fluid that required maintaining the drain for more than 10 days or placing a new one (ultrasound-guided or at operating room).An infection is defined as the need for antibiotics in the first 30 postoperative days. The antibiotic prophylaxis used (Cefazolin the first 24 hours) is excluded.Incidence of residual glandular tissue (Safety). To evaluate the safety of sparing mastectomy through the identification of residual glandular tissue through a magnetic resonance one year after surgery.Incidence of breast cancer relapse (oncological safety). To evaluate the safety of sparing mastectomy through the identification relapses in the same breast during the follow up.Incidence of new breast cancer (safety of risk reducing mastectomy). To evaluate the safety of risk reducing sparing mastectomy in high risk for breast cancer patients through the identification of new breast cancer.Quality of life and satisfaction after a mastectomy with prepectoral reconstruction, using the Breast-Q questionnaire. To assess satisfaction and quality of life after prepectoral reconstruction in women with breast cancer and those with high risk through Breast-Q questionnaire. Also, to identify factors related to satisfaction and quality of life after prepectoral reconstruction (e.g. marital status, psychological illnesses).Incidence of cosmetic sequelae. To evaluate the cosmetic sequelae after prepectoral reconstruction in women with breast cancer and with high risk and Identify factors related to the cosmetic sequelae after prepectoral reconstruction. The investigators will employ the Clough classification, where type I sequelae identified the patients with breast asymmetry but no deformity, type II sequelae were defined by the presence of a deformity that could be corrected using a breast-conserving procedure, and type III sequelae identified those women whose breast showed a deformity or painful fibrosis that could only be solved through mastectomy. To determine the sequelae, the criteria of the breast surgeon will be used, documented through photos.

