#### Breast-Q questionnaire

The Breast-Q questionnaire is aimed at evaluating patient-reported satisfaction and quality of life through the use of breast reconstruction modules. The questionnaires are the intellectual property of the University of Columbia (New York, USA), which freely allows their use for clinical research. The questionnaire is presented in 2 formats: the preoperative format, which is delivered to patients before the surgery, and the postoperative format, which is delivered to them 12–18 months after the surgery. Likewise, we will conduct a second postoperative assessment at 5 years of the surgery. The final score for each module will be calculated according to the Mapi Research Trust criteria [23] and will range from 0 to 100 (the higher the score, the greater the satisfaction and wellbeing).

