The safety assessment of PBR in women with breast cancer requires a minimum follow-up of 5 years. These results will therefore be published 6–7 years after the start of the study. Another secondary objective of the PreQ-20 study is the identification of risk factors for local recurrence after PBR and especially their link with ductal carcinoma *in situ* and the tumor’s biological profile. Another objective will be to detect the onset of primary carcinoma in women with RRM, especially in carriers of the BRCA1 mutation. In our community, 45% of patients with the BRCA1 mutation have an ancestral mutation characteristic of Spain (R71G BRCA1) [24], which has shown greater lethality by promoting a high incidence of triple-negative tumors.

The assessment of RGT with MRI at 1 year of surgery helps determine the incidence rate while simultaneously providing information on the criteria for its assessment and the decision-making process for its follow-up or excision. This new modality for postmastectomy assessment starts a new culture in controlling and following-up sparing mastectomies aimed at the search for RGT.

The quality-of-life assessment in the PreQ-20 study will be conducted using a preoperative survey and 2 postoperative surveys (1 and 5 years after surgery). This methodology differs from most previous studies that only performed 1 postoperative assessment. The comparison between the preoperative and postoperative surveys will help identify those patients who specifically improve or worsen in their satisfaction and wellbeing, which will enable the identification of patient profiles with a higher likelihood of expected improvement or worsening in their satisfaction or wellbeing. By this method, individualized information processes can be established for patients to improve the joint decision-making process. This type of study has already been employed by the authors with women who underwent oncoplastic surgery to identify groups with a greater or lesser benefit for oncoreductive mammoplasty [25].

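### Pre/post Breast-Q change is a stated aim, but the only tests named for quantitative variables are for independent groups and no named method uses the pairing or the baseline score

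*Protocol article*

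**What the plan says.** All references are to the protocol article.

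- **Measurement.** The Breast-Q questionnaire section describes "the preoperative format, which is delivered to patients before the surgery", a postoperative form at 12–18 months, and adds that "we will conduct a second postoperative assessment at 5 years of the surgery". The Discussion sums this up as "a preoperative survey and 2 postoperative surveys (1 and 5 years after surgery". Each module is scored from 0 to 100.
- **Aim.** The objectives list is worded as status after surgery: "To assess satisfaction and quality of life after prepectoral reconstruction in women with breast cancer and those with high risk". The Discussion goes further: "The comparison between the preoperative and postoperative surveys will help identify those patients who specifically improve or worsen in their satisfaction and wellbeing". The Conclusion then places the identification of patient profiles with foreseeable changes in satisfaction and wellbeing among the secondary objectives.
- **Analysis.** Under Statistical analysis, differences between quantitative variables go to Student's "t-test for independent groups. If the conditions of the t-test are not verified, we will use the Mann-Whitney U test". The other methods named are Fisher's exact or chi-squared tests for qualitative variables, and Kaplan-Meier curves with log-rank tests for relapse, new tumours and cosmetic deterioration. The section adds: "Oncological safety and satisfaction assessment will be analyzed by groups: oncological patients and patients with a RRM".
- **Factors.** Outcomes sets out "to identify factors related to satisfaction and quality of life after prepectoral reconstruction (e.g. marital status, psychological illnesses". The list of variables collected for all patients, under Data collection and management, includes neither of these two.

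**The concern.** Three scores from one woman are correlated. A two-sample t-test or Mann-Whitney test treats the preoperative and postoperative scores as coming from different women, so its standard error for the mean change omits the covariance and is wrong. The rule in the Statistical analysis section covers quantitative variables in general, and Breast-Q scores are quantitative. An analyst who follows it as written has no other test to turn to for the pre/post comparison, and nothing that handles three time points together.

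The comparison matters to the study's own case. The Discussion presents repeated assessment as what separates this study from most earlier ones, and the Background faults an earlier study for having no preoperative assessment.

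Comparisons between women, by factor or cancer versus risk-reducing mastectomy (RRM), raise a related point. No named method uses the preoperative score, which would sharpen them and separate a factor's association with outcome from its association with where the women started.

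The two example factors missing from the collection list are a data question and more urgent. The Recruitment section says enrolment has already begun, and a baseline item not recorded at entry is harder to recover later.

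**Working it through.** **The plan's own figure.** The only sample size stated is for implant loss: 5% expected, precision 5 percentage points, 95% confidence, 10% losses (Sample size section).

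n = 1.96² × 0.05 × 0.95 / 0.05² = 72.99, so 73 evaluable. Allowing for losses, 73 × 1.10 = 80.3 (81 rounded up) or 73 / 0.90 = 81.1. The stated 81 reproduces. It does not rest on Breast-Q, so nothing below changes it.

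**Inputs for the check.** The protocol gives no Breast-Q standard deviation, target change or pre/post correlation. Assumptions:
- equal SD before and after, with results in SD units;
- correlation ρ of 0.3, 0.5 or 0.7;
- 73 complete pairs, or 36 per group if the cancer and RRM groups were equal in size (the protocol does not give the split);
- a true mean change of 0.4 SD, for power;
- normal approximation, two-sided 5% level.

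**Formulas.**
- Independent-groups standard error: SE_ind = SD × √(2/n)
- Paired standard error: SE_pair = SD × √(2(1 − ρ)/n)
- Ratio: SE_ind / SE_pair = 1/√(1 − ρ), whatever n is
- Actual type I error of the independent test on paired data: 2 × [1 − Φ(1.96 × ratio)]
- Power of the independent test: Φ[(0.4 − 1.96 × SE_ind)/SE_pair]
- Power of the paired test: Φ[0.4/SE_pair − 1.96]

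**Example, n = 73, ρ = 0.5.** SE_ind = √(2/73) = 0.166; SE_pair = √(1/73) = 0.117; ratio 1.41. Power is Φ[(0.4 − 0.324)/0.117] = 74% for the independent test, against Φ[3.42 − 1.96] = 93% for the paired test.

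| Assumed ρ | SE ratio | Actual alpha | Power at 73 pairs: independent / paired | Power at 36 pairs: independent / paired |
|---|---|---|---|---|
| 0.3 | 1.20 | 0.019 | 71% / 82% | 38% / 53% |
| 0.5 | 1.41 | 0.006 | 74% / 93% | 36% / 67% |
| 0.7 | 1.83 | 0.0003 | 80% / 99% | 32% / 87% |

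At ρ = 0 the two tests agree. At ρ = 0.5 and 73 pairs, the smallest change detectable with 80% power is 0.42 SD (independent) against 0.33 SD (paired). The 36-pair column is relevant because satisfaction is to be analysed separately in the two groups.

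**Comparisons between women.** Adjusting for the preoperative score leaves a fraction 1 − ρ² of the residual variance: 0.91, 0.75 and 0.51 at the same three correlations. That is a reduction of 9%, 25% and 49%.

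**Factors named against variables collected.** Outcomes gives marital status and psychological illness as examples. The collection list covers epidemiological, healthcare, surgical, histological, oncologic, follow-up and Breast-Q variables, and neither factor appears in any group.

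**The case against.** The strongest reply is that the protocol never tells anyone to run an independent t-test on preoperative against postoperative scores. The only satisfaction comparison that the Statistical analysis section spells out is by patient group, where that test is valid. The Discussion can also be read as computing each woman's change and then comparing different women, such as improvers with worseners, and two-sample tests are valid for that too. This stands in part: a reader might infer that the wrong test has been prescribed, but the text supports only that a general rule names independent-groups tests and offers nothing for paired data. The gap remains, because an estimate of mean change within a group still has no suitable method.

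It would also go too far to say that the baseline score is ignored. The Discussion plans to use it; no named method does. Nor do the documents support a claim that the profiles of improvement would be artefacts of regression to the mean, since they do not say whether raw scores or changes will be compared.

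Baseline adjustment has a limit too. The collected modules include satisfaction with information, surgeon, nurses and team, and the protocol does not say that these have a preoperative score. The choice of adjustment could fairly be left to an analysis plan. A named test that does not fit the design is a different matter.

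Finally, the two missing factors are given only as examples, and the collection list is not called exhaustive. That they could not be analysed at all is therefore not shown. The two sections still disagree.

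**Conclusion.** The point holds as a mismatch between a stated aim and the stated methods, and it should be fixed. Followed literally for pre versus post, the rule inflates the standard error of the mean change by 1.20 to 1.83 for an assumed correlation of 0.3 to 0.7. For an assumed 0.4 SD change it costs about 12 to 20 percentage points of power at 73 pairs, and more in the separate groups. With positive correlation the error is conservative: actual alpha falls below 5%, so false positives are not the risk.

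A reader might equate the loss with discarding 30%, 50% or 70% of the women. That is true only of interval width, because the point estimate still uses everyone. Discarding those shares and testing the rest with a paired test gives SE = √(2/n), hence 68% power at 73 pairs against 71%, 74% and 80% for the misapplied test. At 36 pairs it gives 40% against 38%, 36% and 32%. The two are not equivalent in power.

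The issue is confined to a secondary outcome. Implant loss, its analysis and the sample size of 81 are untouched. The sizes rest on the assumed correlation, equal SDs and assumed change; the direction needs only a positive correlation.

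**What to change.** In the Statistical analysis section:

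1. Analyse within-woman Breast-Q change, in the cancer and RRM groups separately, by paired t-test or Wilcoxon signed-rank test, or by one linear mixed model over the three time points. If the mixed model is chosen, state how the rule excluding patients with missing data applies to it.
2. For factor and cancer-versus-RRM comparisons, regress the postoperative score on the factor with the preoperative score as covariate where the module has one. Otherwise analyse it unadjusted.
3. Keep the independent-groups t-test and Mann-Whitney test for comparisons between different women.

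In Data collection and management, add marital status and psychological illness to the list, so that it agrees with Outcomes.

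The cost is a few sentences of analysis text and two baseline fields. Design, visits and sample size do not change, and the statistical package already named can run these analyses. The two fields should be added promptly because recruitment is under way; for women already enrolled, the information would have to be obtained retrospectively.

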### Sample size

According to the meta-analysis by Wagner et al. [1] and the iBRA study [21], the incidence rate of implant loss is 3.3% and 9%, respectively. Our study will therefore assume that a 5% loss of implants would be acceptable and will use this value for calculating the sample size. Therefore, with a 95% confidence level (95% CI), an accuracy of 5% and assuming a 10% of potential losses during follow-up, we estimated that the necessary sample size will be 81 patients.

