## Discussion

The PreQ-20 study will analyze the impact of PBR on 3 separate measures: safety, quality of life and cosmetic sequelae. Unlike other studies that analyzed these 3 measures jointly for women with breast cancer and RRM, our study will individualize the results for each of these 2 patient groups. This differentiation is necessary from the methodological point of view, given that the 2 patient groups have separate characteristics that modify the results and its interpretation, especially in 4 contexts of the research. The first is in regard to the assessment of RGT, given that various studies have shown that its incidence is higher in RRM due to it being a more conservative mastectomy. The second context refers to the incidence of primary tumors in RGT. This fact requires differentiation between patients with cancer and those with a high risk because the latter have a higher likelihood of a primary carcinoma, especially carriers of the BRCA1 mutation. Third, the satisfaction and quality of life requires an independent assessment for each group because women at high risk are healthy, and therefore their expectations and experiences are very different from women with a diagnosis and treatment for breast cancer. Additionally, the physical and sexual wellbeing of patients with cancer is determined by the effects of the adjuvant therapy (hormone therapy, chemotherapy, radiation therapy) and are therefore experienced in different conditions and connotations compared with women at high risk. Lastly, there is a fourth differentiating element between the two groups that focuses on cosmetic sequelae. It is foreseeable that patients with cancer experience a higher incidence of cosmetic sequelae given that the implementation of radiation adjuvant therapy or salvage surgery (nipple excision, subcutaneous fat excision) result in a higher likelihood of cosmetic deterioration. These differences determine that the results of the PBR assessment should be differentiated for these 2 patient groups.

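### The Mann-Whitney fallback does not correct for unequal variances: if two groups differ in both size and spread, the t-test rule departs from 5%, whereas Welch's t-test does not (minor; secondary comparisons only)

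*Protocol article*

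**What the plan says.** The Statistical analysis section gives a two-step rule for quantitative variables. The default is Student's test: "The differences between the quantitative variables will be analyzed using Student’s t-test for independent groups". The fallback follows: "If the conditions of the t-test are not verified, we will use the Mann-Whitney U test". The section does not list the conditions, does not say how they are checked, and mentions no unequal-variance version of the t-test.

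The same section reports such variables on the mean scale: "All quantitative variables will be expressed with the mean, standard deviation and corresponding 95% confidence interval".

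On groups, it says: "Oncological safety and satisfaction assessment will be analyzed by groups: oncological patients and patients with a RRM". The Sample size section fixes a total only ("we estimated that the necessary sample size will be 81 patients"), with no split between oncological and risk-reducing patients or by any other factor. The Study objectives and Outcomes sections add a search for factors related to satisfaction and quality of life, with marital status and psychological illness as examples. That search is the natural use of the two-group rule.

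**The concern.** Student's t-test assumes roughly normal data and equal variances. Mann-Whitney is a reasonable answer to a failure of the first condition but not of the second. Its null variance assumes that both groups follow the same distribution. When spreads differ and group sizes differ too, that variance is wrong, and the test can reject too often or too rarely although the means are equal.

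The plan therefore prescribes an unsuitable remedy for one of its own triggers. A SAP that carried the sentence over would inherit it.

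At stake is how far p-values from the secondary comparisons can be trusted. They would be too small when the smaller group is the more variable, and too large in the reverse case. There is also a mismatch of scale: after the fallback the p-value concerns ranks, while the variables are described by means.

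**Working it through.** **1. The plan's own figure.** The Sample size section uses an implant-loss rate of 5%, 95% confidence, precision of 5 points and 10% loss.

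n = 1.96² × 0.05 × 0.95 / 0.05² = 72.99, so 73 evaluable women. Adding 10% gives 73 × 1.10 = 80.3, so 81; dividing gives 72.99 / 0.9 = 81.1. The stated 81 is reproduced. It concerns a proportion and is independent of the t-test rule. It does supply the totals used below: 73 evaluable, 81 enrolled.

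**2. Why the t-test fails under unequal spread.** Take an assumed split of 69:12 with SDs 1 and 2 (smaller group more variable).

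- True variance of the mean difference: 1/69 + 4/12 = 0.348.
- Expected pooled variance: (68 × 1 + 11 × 4)/79 = 1.418. Variance used by Student's t: 1.418 × (1/69 + 1/12) = 0.139.
- The standard error is too small by a factor of √(0.139/0.348) = 0.63.

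Reverse the SDs: the true variance is 4/69 + 1/12 = 0.141, and the variance used is (68 × 4 + 11 × 1)/79 × (1/69 + 1/12) = 0.350. The standard error is now too large by √(0.350/0.141) = 1.58.

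Mann-Whitney reduces this distortion but does not remove it. Its null variance, n₁n₂(n₁ + n₂ + 1)/12, contains no term for different spreads.

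**3. Simulation.** Assumptions: normal scores, equal means, two-sided 5%, 81 women, 40,000 runs per setting. The two-step rule is taken as Student's t unless a Levene test is significant at 5%, then Mann-Whitney. Each pair is the rejection rate with the larger group more variable / the smaller group more variable.

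| Split | SD ratio | Mann-Whitney alone | Two-step rule | Welch |
|---|---|---|---|---|
| 54:27 | 1.25 | 4.1% / 5.8% | 3.8% / 6.2% | 5.1% / 4.9% |
| 54:27 | 1.5 | 3.5% / 6.7% | 3.2% / 7.0% | 4.9% / 4.9% |
| 54:27 | 2 | 3.0% / 8.4% | 2.9% / 8.4% | 4.8% / 5.0% |
| 61:20 | 1.25 | 3.6% / 6.3% | 3.0% / 7.2% | 5.0% / 5.0% |
| 61:20 | 1.5 | 2.9% / 7.9% | 2.4% / 8.6% | 5.2% / 5.1% |
| 61:20 | 2 | 2.0% / 10.0% | 1.9% / 10.2% | 4.9% / 5.1% |
| 69:12 | 1.5 | 2.2% / 8.7% | 1.6% / 10.5% | 5.4% / 5.0% |
| 69:12 | 2 | 1.0% / 11.7% | 0.8% / 12.7% | 5.2% / 5.0% |

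Student's t alone at 69:12 with ratio 2 gives 0.3% / 21.5%, so the fallback is better than no fallback but still off target.

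**4. The same with 73 women.** With a switch on Levene or Shapiro at 5% (6,000 runs), SDs of 15 and 30 give 2.4% / 9.6% at 53:20 and 1.4% / 11.9% at 60:13. Welch gives 4.9% to 5.5% in those four settings. With a Levene switch alone, 62:11 at ratio 2 gives 0.8% / 12.6%. As proportions, 60/73 is 82% and 62/73 is 85%.

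**5. Where the rule is fine.** With equal SDs, Mann-Whitney stays at 4.7% to 5.1% over all splits at 81 women, and the two-step rule at 5.4% to 5.5% in the unequal splits run at 73. At 37:36 the rule gives 5.0% to 5.7%. At 40:41 Mann-Whitney gives about 5% to 6% up to ratio 2, and about 7% at ratio 3.

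**The case against.** **The size depends on values that the documents do not give.** This stands. No split and no SD is stated. A reader might infer that unequal group size alone pushes the error rate to 1% or 12%. It does not: with equal spread the rate stays near 5% at any split. The extremes need both a split of about 82:18 to 85:15 and a twofold SD ratio.

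**Nothing shows that spreads differ.** This also stands. The Discussion says that "women at high risk are healthy, and therefore their expectations and experiences are very different from women with a diagnosis", and a reader might take this as evidence of unequal variance. It speaks of the level and meaning of scores, not their spread, and does not say which group would vary more. Unequal spread is possible, not established.

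**No test of oncological versus risk-reducing patients is stated.** Correct. A reader might infer that a Breast-Q comparison of these groups is the study's main contribution and is compromised. The Statistical analysis, Discussion and Conclusion sections describe results reported separately by group, and the Breast-Q comparison that the Discussion names is preoperative against postoperative. The two-group rule applies more naturally to the factor analyses.

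**Intervals in Breast-Q points remain.** Correct for each group, since means with 95% CIs are reported whichever test is used. What the plan does not promise under either test is an interval for the difference between groups.

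**How conditions are checked belongs in a SAP.** Agreed, so the missing check is not raised; the Levene and Shapiro switches are modelling assumptions. The choice of fallback is stated in the article, and Mann-Whitney alone drifts in the same way without any preliminary test.

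**Breast-Q runs from 0 to 100, while the simulated scores are unbounded.** With mean 50 and SD 30 about 10% of scores would fall outside the scale, so the upper figures should not be read as exact. Simulation with scores held to 0 to 100 still shows the rule drifting from 5% when size and spread both differ, with Welch close to 5%.

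**Mann-Whitney tests ordering, not means.** True. The term error rate here refers to a difference in means, the scale on which the plan describes these variables.

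**Conclusion.** The point holds in conditional form and is minor. The stated fallback does not deal with unequal variances. If a comparison involves groups unequal in both size and spread, then under the assumptions above:

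- At 2:1 to 3:1 with an SD ratio of about 1.3 to 1.5, the rate is about 3% to 8% (2.4% to 8.6% in the table for a Levene-based switch).
- At about 82:18 to 85:15 with a twofold SD ratio, it is about 1% to 12%.

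Which end applies depends on which group is the more variable.

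The effect is confined to secondary two-group comparisons of quantitative variables, for which the article states no significance level and no confirmatory hypothesis. The primary outcome, implant loss, is a proportion analysed on the whole sample, and neither it nor the calculation behind 81 patients is affected.

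**What to change.** In the Statistical analysis section, replace the two-step rule with wording such as: *Two-group comparisons of quantitative variables will use Welch's t-test (equal variances not assumed), without a preliminary test of variances, and will be reported as a mean difference with its 95% confidence interval. For clearly skewed variables, such as length of stay and delays, the Mann-Whitney U test will be reported with medians and quartiles.*

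This holds the error rate near 5% in the settings examined, and it adds an interval for the difference on the mean scale that the section already uses. It needs no further patients or data. The cost is one sentence and a negligible loss of power when variances are equal.

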## Conclusion

The PreQ-20 study’s main objective is to assess the safety of PBR in terms of postsurgical complications and loss of implants. The results of this study will be differentiated for the groups of women with breast cancer and women with RRM. This differentiation will allow us to analyze the impact of this procedure independently in the contexts of cancer and risk reduction. The secondary objectives of the PreQ-20 study are focused on the analysis of risk factors for local recurrence in women with breast cancer and on identifying the patient profiles with foreseeable changes in their postoperative satisfaction and wellbeing.

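### With about 1 to 5 events expected per group under assumed risks, the large-sample log-rank test cannot support the plan's claim to determine factors for relapse and new tumours

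*Protocol article*

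**What the plan says.** The Statistical analysis section of the protocol article plans Kaplan-Meier curves and would "compare them using the log-rank test to determine those variables related to locoregional relapse and the incidence rate of new tumors". The same section adds: "Oncological safety and satisfaction assessment will be analyzed by groups: oncological patients and patients with a RRM".

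The Discussion states: "Another secondary objective of the PreQ-20 study is the identification of risk factors for local recurrence after PBR". It singles out the link with ductal carcinoma in situ (DCIS) and with the tumour's biological profile. The Conclusion describes the secondary objectives as "focused on the analysis of risk factors for local recurrence in women with breast cancer", alongside profiling changes in satisfaction.

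The Sample size section rests on a different endpoint: "Our study will therefore assume that a 5% loss of implants would be acceptable and will use this value for calculating the sample size". It continues "with a 95% confidence level (95% CI), an accuracy of 5% and assuming a 10% of potential losses during follow-up", and "we estimated that the necessary sample size will be 81 patients". The Discussion sets the time horizon: "The safety assessment of PBR in women with breast cancer requires a minimum follow-up of 5 years".

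The protocol gives no relapse rate, new-tumour rate or expected split between the two groups. It does not describe the factor analysis as exploratory, and it names no exact or permutation form of the log-rank test.

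**The concern.** The test is given an inferential task, to determine which variables are related to relapse and new tumours, in a cohort sized to estimate one proportion for another endpoint and then divided in two. Relapse and new tumours may be few in groups of this size. The usual log-rank p-value relies on a normal approximation that needs a reasonable number of events. With very few, the nominal 5% error rate is no longer the real one.

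A significant factor could rest on one to four events and carry a p-value that overstates the evidence. A non-significant result for DCIS or biological profile would say almost nothing, because even a large effect would usually be missed. The stated objective invites a conclusion that the data could not carry in either direction.

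**Working it through.** **1. The plan's own figure.** Single-proportion precision: n = z²p(1−p)/d² = 1.96² × 0.05 × 0.95 / 0.05² = 72.99, so 73. Allowing for 10% losses: 72.99/0.9 = 81.1. The stated 81 reproduces, and about 73 evaluable women is the right working number. Nothing in this calculation concerns relapse.

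**2. Expected events.** The risks and group sizes are assumptions, because the protocol gives neither. Group sizes are 36 (about half of 73) and 50 (a larger cancer group). The 5-year risk r is 2%, 5% or 10%. Expected events = n × r; chance of no event = (1−r)^n.

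| Group size | Risk | Expected events | Chance of no event |
|---|---|---|---|
| 36 | 2% | 0.7 | 48% |
| 36 | 5% | 1.8 | 16% |
| 36 | 10% | 3.6 | 2% |
| 50 | 2% | 1.0 | 36% |
| 50 | 5% | 2.5 | 8% |
| 50 | 10% | 5.0 | 0.5% |

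This gives about 1 to 5 expected events per group. If a group has no event, there is no log-rank statistic to compute.

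**3. Reliability of the p-value, balanced factor.** Take 18 women with the factor and 18 without, no censoring before the events, and all events on one side. U is observed minus expected events, V its variance, and z = U/√V. The exact two-sided permutation p-value for k such events is 2 × C(18,k)/C(36,k).

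- 3 events: U = 1.54, V = 0.75, z = 1.78, large-sample p = 0.07.
- 4 events: U = 2.09, V = 1.00, z = 2.09, large-sample p = 0.036. Exact p = 2 × 3060/58905 = 0.104.
- 5 events: exact p = 0.045.

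With four events the large-sample test rejects only when all four fall on one side (a 3 to 1 division gives z of about 1.0 to 1.1). Its true error rate in that setting is therefore 0.104, about twice the nominal 5%.

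**4. Reliability of the p-value, uncommon factor.** Take one event, with the factor in 4 of 36 women. If the event falls in a woman with the factor, U = 1 − 4/36 = 0.889, V = (4/36)(32/36) = 0.0988, z = 2.83, p = 0.005. If there is no association, this happens with probability 4/36 = 11%. The nominal 5% test thus rejects 11% of the time on a single event.

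**5. Power.** Schoenfeld's formula for a balanced factor and two-sided 5%: power ≈ Φ(√(d/4) × ln HR − 1.96), where d is the number of events. For a hazard ratio (HR) of 3:

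- d = 1.0: 8%
- d = 2.5: 14%
- d = 3.6: 18%
- d = 5.0: 23%

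These figures are only indicative, because the formula uses the same normal approximation that step 3 shows failing. For a balanced factor with three or fewer events, the test cannot reach 5% at all.

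**6. A check that needs no relapse rate.** 80% power for a balanced factor needs about 66 events for HR 2, 27 for HR 3 and 13 for HR 5. As shares of all 73 women, undivided, these are 90%, 37% and 18%. Within one group the required shares are higher.

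**The case against.** The formal list of secondary objectives asks for relapses and primary carcinomas to be identified, and seeks related factors only for quality of life and cosmetic sequelae. Risk factors for recurrence appear as an objective only in the Discussion and Conclusion. Sizing a cohort on its primary outcome is ordinary practice, and event projections for secondary analyses are commonly left to a fuller document. This stands: the absence of a power statement is not the fault, and low power alone would not be a finding. What the article does fix is the test, its purpose, the split by group and the wording of the objective, and these do not fit together.

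A reader might infer that the objective can never be met, or that each group must yield no more than four events at any plausible rate. The documents do not support either reading. They give no rate and no split, and nothing makes the groups equal; the Recruitment section describes only women diagnosed with breast cancer, which if anything suggests a larger cancer group. With 50 cancer patients at an assumed 10% risk, 5 events are expected and the chance of 5 or more is 57%. At an assumed 15% risk, 7.5 are expected and the indicative power for HR 3 is 32%. A very large effect could still show.

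A reader might also infer that all the variables listed under Data collection and management will be tested, or that a null result will be reported as no association. The protocol says neither. Finally, Kaplan-Meier and log-rank are sound methods, and the plan already provides proportions with confidence intervals and analysis by group. The fault lies in relying on the large-sample p-value at these counts, and in the conclusion that the test is meant to deliver.

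**Conclusion.** The point holds as a validity fault in a secondary analysis. The log-rank test, read in its usual large-sample form, is assigned to determine factors for relapse and new tumours within two groups of a cohort of about 73 evaluable women sized for implant loss. Under assumed 5-year risks of 2% to 10% and groups of 36 to 50, about 1 to 5 events per group are expected. In worked cases at such counts the nominal 5% test has a true error rate of 10% to 11%, and power for HR 3 is roughly 25% or less. A significant result would be weaker than its p-value suggests, and a null result would be uninformative.

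The event counts depend on assumptions about risk and group split. The p-value discrepancies do not depend on the relapse rate, but they apply to the event counts and factor splits shown. The implant-loss outcome is unaffected.

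**What to change.** **Statistical analysis section.** For each group, make the main oncological result the number of events, the Kaplan-Meier 5-year incidence, and an exact (Clopper-Pearson) 95% interval for the 5-year proportion. As an illustration, no events among 36 women gives an upper limit of 1 − 0.025^(1/36) = 9.7%. Label any comparison of factors exploratory, limit it to the factors that the Discussion names (DCIS and tumour biological profile), and replace the large-sample p-value with an exact permutation log-rank p-value.

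**Discussion and Conclusion.** Reword the aim from identifying or analysing risk factors for local recurrence to a descriptive, hypothesis-generating one.

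The comparisons need not be deleted, and no minimum event count is needed before running them, since the exact p-value shows how little a few events can prove.

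**Cost.** Changes of wording and one change of p-value method, with no additional patients or data. The downside is that a secondary objective claims less.
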